### Intervention

The intervention consists of an IVRS call coupled with pharmacist support. We will program the IVRS to call patients automatically on day 3 and day 17 following their prescription. If a call is not answered, the system will make as many as eight separate attempts (two per day over a maximum of 4 days) before marking the call as unsuccessful. If a call is answered, the IVRS will proceed through a calling algorithm. The following questions will be asked at each call:Since receiving your medication, have you started taking it?Since receiving your medication, have you had any problems?Since receiving your medication, have you developed any new symptoms?Would you like to speak to a pharmacist?

If the patient answers ‘No’ to the first question or ‘Yes’ to any of the three remaining questions, the IVRS will inform the patient that a pharmacist will personally contact them within 2 business days. The IVRS will send an email to a pharmacist informing them of the patient’s request. In addition, the IVRS will be capable of receiving inbound calls from patients regarding their medications at any time. This will also connect the patient to the pharmacist according to the same business rules as for the outbound IVRS calls.

When required, the pharmacist will contact the patient. Prior to contact, the pharmacist will access the electronic health record to obtain background information on the patient’s health status and medication use. During the call, the pharmacist will document the patient’s problems as well as their recommendation for resolving the problem in the electronic health record. If the pharmacist deems the patient’s problems are significant, then the pharmacist can escalate the issue to the patient’s primary care physician using the electronic health record.

### Control

The control arm consists of routine care.

### Instrumentation

#### Interview at 21 days

We will perform a standard interview of patients at 21 days to determine the development of new symptoms, medication use and health services use since their prescription. The study personnel performing the interview will not have access to knowledge regarding the study group to which the patient is allocated.

#### Administrative database interrogation

We will link the study database to the drug benefit and hospital record files contained at RAMQ using the patient’s provincial health insurance number.

### Outcome assessment

#### Primary outcome: medication persistence at 180 days

We define persistence as ‘having a continuous supply of at least one medication used to treat the index condition, with gaps no greater than 90 days, in the first 6 months of treatment’. We will use validated methods to measure medication persistence using administrative claims data on prescription refills
[7–11]. Prescription refills provide a good proxy measure of medication use because refill rates are strongly correlated with targeted clinical outcomes such as blood pressure
[7]. We will construct medication dispensing histories for all patients and medications during the study follow-up period using the RAMQ medication file.

#### Secondary outcome: ADEs within 21 days

We will use previously developed methods to ascertain ADE status
[12–17]. Specifically, a clinician will create a case summary describing the post-prescription course for each patient experiencing a problem. Problems will be identified during the 21-day interview. The clinician will compile information derived from the post-intervention interview and a review of the patient’s MOXXI record using a standardized format. The summary will elaborate on the patient’s underlying health conditions, the medications currently being used (including the index prescription), the timing of the problem, the management of the problem, the timing of the resolution and what the patient was told about the cause of the problem.

To define ADE status, two physicians (blinded to allocation group) will review each case summary and determine whether the case represents an ADE. This determination is made using a six-point classification system with a cut-point of 3. A case is considered to be an ADE if both reviewers agree that the case was an undesirable outcome and that outcome was more likely caused by medication use than the patient’s underlying health condition. This method has been widely adopted as the standard approach for ADE classification in patient safety research
[12–17]. For an ADE, the reviewers will further classify its duration, preventability, amelioration and severity using standard definitions
[12–19].

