### Setting

This research will occur during ambulatory care in the province of Québec, Canada. We will study prescriptions in patients receiving primary care from a selected group of physicians using the Medical Office of the 21st Century (MOXXI) electronic health record system. MOXXI was developed by the McGill University’s Clinical and Health Informatics Research Group. It is currently used by over 100 primary care physicians in Montréal and Québec City. The MOXXI system is linked to the provincial insurance company, Régie de l’assurance maladie du Québec (RAMQ), resulting in an electronic medical record that displays a drug profile of prescribed as well as dispensed drugs, emergency department visits and hospitalizations in the past 12 months, a list of active and past health problems, and an electronic prescribing tool. Data stored by MOXXI have been used by the McGill research team for medical research in the past
[3, 4].

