### Secondary objectives

Determine whether the ISTOP-ADE system, compared to routine care, will reduce the probability of a patient experiencing a severe ADE (defined as an ADE lasting at least 7 days or causing an emergency department visit).Determine whether the ISTOP-ADE system, compared to routine care, will reduce the proportion of patients experiencing ADEs, preventable ADEs and ameliorable ADEs.Determine whether the ISTOP-ADE system, compared to routine care, will reduce health services utilization (comprising physician visits, emergency department encounters and hospitalizations) at 12 months following an incident prescription.Measure the costs associated with the ISTOP-ADE system.

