#### Health services utilization

Standard methods to measure health services use using provincial claims data will be used. All physician visits, emergency department visits, hospitalizations and medication claims during the 12 months following index prescription will be identified using the RAMQ data through MOXXI.

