### Sample size

We have based our sample size on the following assumptions:A baseline probability of non-persistence of 25% (based on a prior research study evaluating persistence with anti-hypertensive therapy using the same methods we will for this study) [11]A minimally clinical important difference of 20%A 10% loss to follow-up (based on our pilot study)An enrollment rate of 50% (based on our pilot study)Other specifications: α = 0.05, β = 0.20 and two-sided tests for significance will be used

Given these assumptions, we will need to approach 4,708 patients in total (2,354 patients in each treatment arm being eligible and approached for enrollment). This will result in 2,354 patients being enrolled (1,177 patients in each arm) and 2,118 patients evaluated for the composite outcome (1,059 patients in each arm). To be more conservative, we will enroll 1,100 patients in each arm.

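### The 21-day interview is the only stated way to find an ADE case, so some emergency-visit or admission ADEs can go unreviewed although the visit data are already held

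*Protocol article*

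**What the plan says.** The section on ADEs within 21 days sets out a chain:

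- **Who gets a summary:** "a clinician will create a case summary describing the post-prescription course for each patient experiencing a problem".
- **How a problem is found:** "Problems will be identified during the 21-day interview".
- **What the record is for:** "The clinician will compile information derived from the post-intervention interview and a review of the patient’s MOXXI record using a standardized format".
- **Who decides:** two physicians, blinded to arm, review each case summary.

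The section on the interview describes its content: "We will perform a standard interview of patients at 21 days to determine the development of new symptoms, medication use and health services use". It does not state how the interview is conducted.

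The secondary objectives describe a severe ADE as "defined as an ADE lasting at least 7 days or causing an emergency department visit". Visit data appear elsewhere for other purposes. Under Setting, MOXXI displays "emergency department visits and hospitalizations in the past 12 months". Under Administrative database interrogation, the study database is linked to RAMQ drug benefit and hospital files. Under Health services utilization, "All physician visits, emergency department visits, hospitalizations and medication claims during the 12 months following index prescription will be identified".

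**The concern.** A case that never enters the chain cannot be recovered by careful, blinded adjudication later. If the only way in is an interview with the patient, an event that keeps the patient from being interviewed also removes itself from the count, as does an event the patient does not mention. The first two secondary objectives (severe ADE; any, preventable and ameliorable ADE) depend on this chain. The severe outcome includes emergency visits, and the article's abstract names fewer ADEs leading to an emergency or inpatient encounter as an expected benefit. These are the events for which the trial has a second source, and the plan does not use that source to find cases.

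**Working it through.** The protocol gives no figure to reproduce on this point, so the check is mainly a reading of the sections together.

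**Step 1: can a patient without an interview become an ADE case?** No interview means no identified problem, hence no case summary and nothing for the two physicians to review. The MOXXI record enters only when a summary is compiled, so it adds detail to cases already found. On the stated text the answer is no.

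**Step 2: can an interviewed patient's visit be missed?** The interview asks about health services use, so a patient discharged before day 21 can report the event. If the patient does not, no stated step compares the answer with the record.

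**Step 3: do the data to close the gap exist?** Emergency visits and hospitalizations are displayed in MOXXI and retrieved from RAMQ for 12 months after the index prescription. Eligibility requires patients to use RAMQ insurance for their medications. The documents mention no death data.

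**Step 4: scale, as an illustration only.** Let *m* be the share not interviewed and *r* the risk of a severe ADE in uninterviewed relative to interviewed patients. Suppose every interviewed patient reports fully.

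Share of severe ADEs missed = *m·r* / [(1 − *m*) + *m·r*]

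Rate seen among interviewed patients ÷ true rate = 1 / [(1 − *m*) + *m·r*]

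Take *m* = 0.10. This is an assumption: the 10% loss in the Sample size section is an input to a calculation built on non-persistence and is not tied to the interview. It would mean 0.10 × 1,100 = 110 patients per arm, 220 in all.

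| *r* | Share missed | Interviewed-only rate ÷ true rate |
|---|---|---|
| 1 | 0.10/1.00 = 10% | 1/1.00 = 1.00 |
| 2 | 0.20/1.10 = 18% | 1/1.10 = 0.91 |
| 3 | 0.30/1.20 = 25% | 1/1.20 = 0.83 |

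If the true severe-ADE rate were between 2% and 10% (also assumed), the missed events over 2,200 patients would run from 2,200 × 0.02 × 0.10 = 4.4 to 2,200 × 0.10 × 0.25 = 55. At *r* = 1 an interviewed-only rate is unbiased and the cost is lost information. The rate is understated only if *r* exceeds 1, and the documents do not give *r*.

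**The case against.** **Stronger readings that the text does not support.**

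- A reader might infer that the most serious ADEs are lost as a class. They are not: patients seen and discharged before day 21 can report the event, because the interview covers health services use.
- A reader might infer that the loss is concentrated in severe ADEs. The definition also covers any ADE lasting at least 7 days, which need not stop an ambulatory patient from being interviewed.
- A reader might infer that the two arms lose cases unequally. Intervention patients have a second round of automated calls from day 17, with attempts over at most 4 days, so up to day 20, and controls have none. A difference in interview response is conceivable, but the interview mode is not stated and nothing fixes even the direction.
- A reader might take the 10% loss as the expected rate of missed interviews. The article does not say so.

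**Is this only an article's brevity?** Interview windows, repeat attempts, proxies and late interviews may well sit in the full protocol, and their absence here is not criticised. What remains is a stated rule: the article says where problems are identified and gives the record a later role. More interview attempts would reduce the gap but would not add a second route.

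**Are the events visible anyway?** Emergency visits and hospitalizations are counted as utilization in both arms. That stands, but those counts are not reviewed for drug causation and do not feed the ADE outcomes.

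**Would a record trigger bring its own problems?** Yes. Summaries without an interview will be thinner on timing, resolution and what the patient was told. Counting all uninterviewed patients as free of severe ADE would misclassify those with a long-lasting problem and no visit. Both points stand and shape the fix.

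**Conclusion.** The point holds in a limited form. As written, the 21-day interview is the sole stated entry to ADE review, so ADEs leading to an emergency visit or admission can be missed in patients who are not interviewed or do not report them, while the trial already holds the visits. That some severe ADEs can be missed follows from the stated route together with the definition of a severe ADE. How many, and whether the arms differ, cannot be computed from the documents. The 10% to 25% range rests on an assumed 10% without interview and an assumed relative risk of 1 to 3. Secondary outcomes are affected; the primary outcome, persistence from claims, is not. The change is worth making because it is cheap, not because a large bias has been shown.

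**What to change.** In the section on ADEs within 21 days, add a second trigger:

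1. Write a case summary for every randomised patient with an emergency department visit or hospitalization within 21 days of the index prescription in MOXXI/RAMQ, whether or not interviewed. Include death if the linked data record it.
2. Apply the same rule in both arms. Remove pharmacist-contact notes before review: the Intervention section has the pharmacist document calls in the electronic health record, which would reveal allocation.
3. Send these summaries to the same two blinded physicians under the same classification.
4. Show interview-triggered and record-triggered cases separately, so that results remain comparable with the interview-based method.
5. Report the emergency-visit component of severe ADE over all randomised patients. Report the component lasting at least 7 days, and the other ADE outcomes, among interviewed patients, with uninterviewed patients treated as missing rather than event-free.

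The cost is a query of data the trial already links and a modest number of extra summaries, with less detail where there was no interview. The change does not recover long-lasting ADEs without a visit in uninterviewed patients.

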### Blinding

Due to the nature of the study, blinding of patients and health-care providers will not be possible. However, we will blind personnel performing the interviews and physicians performing the assessment of ADE status of study group allocation.

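### ADE case summaries draw on a record that holds study-pharmacist entries for intervention patients only, so the blinded review of the secondary ADE outcomes is not protected as written

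*Protocol article*

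**What the plan says.** The statements that matter are spread over several sections of the protocol article.

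- **Setting** describes MOXXI as the "Medical Office of the 21st Century (MOXXI) electronic health record system". No other record system is named.
- **Intervention**: after an automated call on day 3 or day 17 triggers contact, "the pharmacist will document the patient’s problems as well as their recommendation for resolving the problem in the electronic health record". In addition, "the pharmacist can escalate the issue to the patient’s primary care physician using the electronic health record".
- **Control** is routine care, and **Intervention costs** ties the study pharmacist's time to the intervention group.
- **Secondary outcome: ADEs within 21 days**: problems are picked up at the 21-day interview. A clinician will then "compile information derived from the post-intervention interview and a review of the patient’s MOXXI record", in a standardized format. The required content includes management of the problem, "the timing of the resolution and what the patient was told about the cause of the problem". Two physicians, described as blinded, judge ADE status from that summary and then rate duration, preventability, amelioration and severity.
- **Blinding**: "we will blind personnel performing the interviews and physicians performing the assessment of ADE status of study group allocation". The clinician who reads the record and writes the summary is not mentioned.
- **Discussion** relies on objective or blinded outcome assessment as the answer to the lack of blinding of patients and doctors.

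**The concern.** The intervention leaves a written trace in the same record from which the outcome assessment is built, and it does so in one arm only. Two problems can follow for patients who had pharmacist contact. First, a summary that reports a pharmacist's call, advice or escalation can reveal the arm to the reviewers. Second, the reviewers may have a contemporaneous professional account of timing and likely cause that has no study counterpart in controls. An ADE verdict needs both reviewers to agree that the drug was the more likely cause, so fuller documentation may make agreement easier in one arm.

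What is at stake is the adjudicated part of the secondary objectives: any ADE, severe ADE, preventable ADE and ameliorable ADE. A bias of unknown sign in the adjudication cannot be removed at the analysis stage.

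**Working it through.** No figure in the protocol belongs to this point. The main check is a cross-reading; the arithmetic is an illustration on assumed inputs.

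**Information flow**

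1. Who generates the entries: the study pharmacist, who supports intervention patients only (Intervention, Control, Intervention costs).
2. Where they go: the electronic health record (Intervention). The Setting section identifies MOXXI as that record. The Intervention section does not repeat the name, so this step is an inference, but no alternative is offered.
3. When: outbound calls are on days 3 and 17, before the day-21 interview, so entries can already exist when the summary is written.
4. What the summary takes: interview plus MOXXI record, including management and what the patient was told. These are the items a pharmacist call produces.
5. What stands between the entries and the reviewers: a standardized format and a summary writer. No removal or masking of entries is stated, and the writer is not listed as blinded.
6. What the notes cannot do: create a case. Entry to case review is through the 21-day interview, done in both arms by blinded personnel. Any bias therefore arises in the adjudication of cases already found.

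**Assumed illustration**

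Inputs from the protocol: 1,100 enrolled per arm and 10% loss, so 1,100 × 0.90 = 990 per arm; two-sided α = 0.05, chi-square test. Inputs assumed, because the protocol gives no ADE risk or detection rate: true ADE risk 20% in both arms, no false positives, detection 80% in controls.

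A rough ceiling for detection in the intervention arm can be built from the pilot figure in the Background section, where the system identified 45% of ADEs. Suppose those 45% were all adjudicated correctly and the other 55% stayed at the control rate:

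- from 80%: 0.55 × 80 + 0.45 × 100 = 89%
- from 70%: 0.55 × 70 + 0.45 × 100 = 83.5%

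Apparent risk = true risk × detection. The rejection rate is the normal approximation to the chi-square test at 990 per arm.

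| Detection, control vs intervention | Apparent risk | Apparent risk ratio | Rejection with no true effect |
|---|---|---|---|
| 80% vs 85% | 16.0% vs 17.0% | 1.06 | about 9% |
| 80% vs 89% (ceiling) | 16.0% vs 17.8% | 1.11 | about 19% |
| 70% vs 83.5% (ceiling) | 14.0% vs 16.7% | 1.19 | about 38% |

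The nominal rate is 5%. If there were a true 20% relative reduction (16% against 20%), the first two rows would give 0.16 × 0.85 = 13.6% and 0.16 × 0.89 = 14.2% against 16.0%. The apparent reductions would be 15% and 11%.

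These rows cover unequal detection only, which works against the intervention. The effect of reviewers knowing the arm could go either way and is not modelled.

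**The case against.** Several points on the other side are sound.

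- **Case finding is symmetric by design.** The same blinded interview triggers review in both arms. A reader might infer that pharmacist notes add ADE cases in the intervention arm; the text rules that out. This limits the concern to adjudication.
- **The reviewers see a summary, not the record.** A reader might conclude that they will certainly know the arm, or that the blinding claim is false. The documents do not support that. A standardized format could hide the source, the full protocol may contain a masking step, and silence about the summary writer does not mean that the writer knows the arm. Control patients may also have had advice from their doctor or dispensing pharmacist, so a mention of professional advice does not identify the arm by itself. What stands against this is that the article does spell out the sources, the required contents and the blinded roles. Followed as stated, they carry intervention content to the reviewers with nothing to stop it.
- **A large bias is not established.** It is tempting to assume 70% against 90% detection, which would give 14% vs 18% and rejection in about 68% of trials with no true effect. That exceeds the 83.5% ceiling above, and even the ceiling needs perfect adjudication of every ADE the system identified.
- **The main outcomes are safe.** Persistence and health services use come from RAMQ data and do not pass through this review.
- **Removing the item on what the patient was told would change an adjudication method that the protocol presents as established.** This is accepted, and the remedy below keeps that item.

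**Conclusion.** The point holds in a limited form. As written, the plan lets study-pharmacist and escalation entries, which exist in one arm only, reach the summaries on which ADE status, duration, preventability, amelioration and severity are judged. The blinded review that the Discussion relies on is therefore not shown to be protected for the secondary ADE outcomes. Only intervention patients with pharmacist contact are affected, and only at adjudication.

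The direction is uncertain: fuller documentation would tend to raise the ADE count in the intervention arm, while knowledge of the arm could move the ratings either way. The size cannot be set from the documents. At an assumed 20% true risk, 80% against 85% to 89% detection gives a spurious risk ratio of about 1.06 to 1.11. The conclusion rests on reading the electronic health record in the Intervention section as MOXXI, and on there being no masking step in a fuller document. It does not extend to the primary outcome or to utilization.

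**What to change.** Before the first case is summarized:

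1. In both arms, compile the summary from the 21-day interview plus a MOXXI extract from which ISTOP-ADE pharmacist notes, IVRS entries and pharmacist-to-physician escalation messages have been filtered out by program.
2. Keep the fields on management and on what the patient was told, filled from the interview or routine-care notes, but worded without the source so that study-pharmacist contact cannot be recognized.
3. Give the summary writer only this extract, and add that role to the Blinding section.

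The cost is a filter on note author and type and an edit to the summary template. The real downside is that some management detail is lost for intervention cases, which matters most for the preventability and amelioration ratings. The protocol should acknowledge this. Since the article states that the trial has not started, the change is cheap now; later it would mean abstracting and reviewing cases again.
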